### Sample size and statistical considerations

In the present study, 125 subjects will be recruited, randomized according to a 1:1 ratio in the intervention and the control arm. To find a significant difference in cholesterol levels between the two treatments (BruMeChol™ vs. placebo) at the end of the 2nd follow-up, assuming a medium effect size of the proposed treatment (*d* = 0.5), we should study at least 118 subjects (at least 59 for treatment arm) with a power of 0.85 and a type I error probability of 0.05. By providing a dropout rate of 5%, a total of 125 participants must be recruited.

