### Outcomes

#### Primary outcome

The primary outcome is the change in serum total cholesterol levels after 12 weeks of post-intervention commencement between experimental arm and placebo comparator arm.

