##### Biochemical profile

Screening visit will include following measurements: total cholesterol, fasting glucose, liver profile (AST/GOT, ALT/GPT), kidney profile (creatinine, CKD-EPI e-GFR) and thyrotropin (TSH). Serum lipid profile: total, LDL, HDL cholesterol and triglycerides, liver profile (AST/GOT, ALT/GPT), kidney profile (creatinine, CKD-EPI e-GFR), fasting glucose, fool blood exam (FBE), leukocyte formula, electrolytes, cardiac/muscular markers (CK/myoglobin), CRP, and Lp(a) will be measured at baseline, 6 weeks, and on completion of the study (12 weeks from randomization). All items that will be measured at every visit are described in Table 2.

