### Retention

During the study, the participants will be encouraged by the physician to complete the follow-up. However, in case they still cannot complete the study, the motive for their withdrawal will be registered.

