### Statistical analysis

Demographic, clinical characteristics and outcomes data will be summarized with counts and percentages for categorical variables, means (standard deviations) for normally distributed continuous variables, and medians (with interquartile ranges) for other continuous variables. Kolmogorov-Smirnov test will be used to check the normality of the related variables. Repeated measures analysis of variance (ANOVA) will be used to test whether treatment (between-subjects factor) differentially affect the mean values of cholesterol levels (within-subjects factor) over time. The same analysis will be also repeated for the inflammatory biomarkers that will be used as within-subjects’ factors. Mauchly’s test will be used to assess the assumption of sphericity, and Greenhouse-Geisser correction will be adopted for violations of this assumption. A significant level of 0.05 will be used throughout the study. Statistical analyses will be performed with IBM SPSS statistical software ver. 25.0 (IBM Corp., Armonk, NY, USA).

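### Unless missing values are imputed first, the planned repeated-measures ANOVA drops subjects whose 12-week outcome is known; a mixed model in the same software would keep them

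*Protocol article*

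**What the plan says.** All references are to the protocol article.

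- **Method (Statistical analysis).** "Repeated measures analysis of variance (ANOVA) will be used to test whether treatment", the between-subjects factor, changes mean cholesterol over time. The same analysis is to be repeated for the inflammatory biomarkers.
- **Sphericity (same section).** Mauchly's "test will be used to assess the assumption of sphericity, and Greenhouse-Geisser correction will be adopted for violations of this assumption".
- **Software (same section).** "Statistical analyses will be performed with IBM SPSS statistical software ver. 25.0".
- **Visits (Biochemical profile).** Total cholesterol, with the other laboratory values, "will be measured at baseline, 6 weeks, and on completion of the study (12 weeks from randomization"). Table 2 agrees.
- **Outcome (Primary outcome).** "The primary outcome is the change in serum total cholesterol levels after 12 weeks of post-intervention commencement", compared between the arms. The sample size section also powers the comparison at the second follow-up.
- **Dropout (Sample size and statistical considerations).** At least 118 subjects are needed, 59 per arm. "By providing a dropout rate of 5%, a total of 125 participants must be recruited".
- **Withdrawals (Retention).** "in case they still cannot complete the study, the motive for their withdrawal will be registered".

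The article names no imputation step and no alternative model that would use partial records.

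**The concern.** The primary outcome needs two values per subject, baseline and week 12. The method fixed for it needs three. A sphericity test has content only with three or more time levels, so the within-subject factor must be baseline, week 6 and week 12. The SPSS procedure that produces Mauchly and Greenhouse-Geisser output reads one row per subject and leaves out any row with a gap.

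Two kinds of subject are affected:

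1. A subject who misses only week 6 has an observed primary outcome and is still excluded.
2. A subject who leaves after week 6 has no 12-week value, but does have a week-6 value that carries information about it. That value is discarded.

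At stake are some precision and, more importantly, comparability. The analysed arms would be those who attended every visit. If leaving is related to cholesterol already observed, for example a disappointing week-6 result, those arms may differ from the arms that were randomised.

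**Working it through.** **Inputs from the article:** d = 0.5, power 0.85, type I error 0.05, 1:1 allocation, 118 evaluable, 5% dropout, 125 recruited. **Assumed, because not given:** the share m missing only week 6 among subjects who have week 12, taken as 0% to 10%.

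**Step 1. Reproduce the plan's figures.** A two-sample t-test with d = 0.5, power 0.85 and one-sided alpha 0.05 needs 58.2 per arm, so 59 per arm and 118 in all, as stated. A two-sided test would need 73 per arm (146). For dropout, 118 / 0.95 = 124.2, so 125, as stated.

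**Step 2. The slack.** Expected with a 12-week value: 125 × 0.95 = 118.75, against 118 required. The margin is less than one subject.

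**Step 3. Complete cases.** N = 125 × 0.95 × (1 − m). Power is from the noncentral t distribution with n = N/2 per arm and noncentrality 0.5 × √(n/2). At m = 0 that is 0.5 × √(59.375/2) = 2.72; at m = 5% it is 0.5 × √(56.41/2) = 2.66.

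| m | N analysed | Lost to a missing week 6 | Power, one-sided | Power, two-sided |
|---|---|---|---|---|
| 0% | 118.8 | 0 | 0.856 | 0.771 |
| 2% | 116.4 | 2.4 | 0.850 | 0.762 |
| 5% | 112.8 | 5.9 | 0.840 | 0.749 |
| 10% | 106.9 | 11.9 | 0.822 | 0.726 |

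Read down one column at a time. At m = 5% the loss is 0.856 − 0.840 = 0.016 one-sided or 0.771 − 0.749 = 0.022 two-sided. At m = 10% it is 0.034 or 0.045. An analysis that keeps every available 12-week value retains about 118.75 subjects in each row.

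These are t-test powers, used because they match the plan's own calculation. They are not powers for the ANOVA interaction or for a mixed model.

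**Step 4. Recruitment that would keep 118 complete cases.** 118 / (0.95 × 0.95) = 130.7, so 131 at m = 5%. 118 / (0.95 × 0.90) = 138.01, so 139 at m = 10%. The analysis change avoids this.

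**Step 5. Scope for selection among leavers.** If a share p of an arm leaves, the mean of those who stay differs from the whole-arm mean by p × (mean of stayers − mean of leavers). The plan expects 125 − 118.75 = 6.25 leavers. If all were in one arm of 62.5, p = 6.25 / 62.5 = 0.10, so that arm's mean would shift by a tenth of the stayer-leaver difference. If leavers are equal in number and kind in both arms, the shifts cancel. How many would leave after week 6, and why, is unknown.

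**The case against.** **Exclusion is inferred.** No sentence in the article says that subjects with a missing visit are left out. It follows from the named procedure, and imputation in a full protocol or analysis plan not shown here would remove it. This stands, and is why the point is conditional. A reader might infer that the trial has no plan for missing data. The article does not support that, because a condensed article commonly leaves such detail to the full document. The point concerns the method that is named.

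**The power effect is small.** This also stands. A reader might set the two-sided 0.75 at 5% missing against the planned 0.85 and blame the ANOVA for the gap. Only about 0.02 is due to excluded subjects. The rest arises because 118 matches a one-sided test, which is a separate matter.

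**The selection argument has limits.** A reader might infer that the complete-case comparison is valid only if data are missing completely at random. That is too strong: if missingness depends on arm alone, the mean change within each arm, and so the contrast, is still unbiased. Nor can a week-6 result explain the absence of someone who missed week 6. That mechanism applies only to those who leave afterwards, and they have no 12-week value under any method. A mixed model recovers part of their information, through the correlation between visits.

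**The remedy is not perfect or unique.** A set defined by any post-baseline value also depends on events after randomisation, although it excludes fewer subjects. Baseline-adjusted ANCOVA at week 12 would likewise keep everyone with a 12-week value, but would not use the week-6 values of those who leave.

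**The supporting sections are sound in themselves.** The dropout inflation is correct arithmetic and does not say who is analysed. Recording reasons for withdrawal is good practice.

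**Conclusion.** The point holds in conditional form. As written, and unless values are imputed first, the primary analysis excludes subjects whose primary outcome is observed and ignores week-6 data from later leavers, while the sample size leaves less than one subject to spare.

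The cost in power is modest: about 0.02 at an assumed 5% missing week 6, up to 0.034 one-sided or 0.045 two-sided at 10%, and none at 0%. The larger concern is selection if missingness depends on observed cholesterol. Its size cannot be computed from the article, and under the plan's own 5% dropout its scope is limited.

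The conclusion rests on the article's 5% dropout, the assumed range for m, the plan's d = 0.5, and the known behaviour of the SPSS repeated-measures procedure. This is a conventional method with a known weakness and a nearly free improvement; it does not invalidate the trial.

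**What to change.** In the Statistical analysis section, replace the repeated-measures ANOVA with a likelihood-based linear mixed model (SPSS MIXED):

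- **Response:** total cholesterol at weeks 6 and 12.
- **Terms:** treatment, visit, treatment-by-visit and baseline cholesterol, with unstructured covariance between visits.
- **Subjects:** all randomised subjects with any post-baseline value, in their allocated arm.
- **Primary result:** the between-arm contrast at week 12, which is the stated primary outcome.
- **Biomarkers:** the same model for the inflammatory biomarkers.
- **Drop:** Mauchly's test and the Greenhouse-Geisser correction, which an unstructured covariance makes unnecessary.

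The cost is new analysis wording and a different procedure in the same software, with no new data or visits. The model still relies on missing at random given baseline and the observed visits. It does not protect against leaving for reasons that those values do not capture.

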### Data and biological sample handling

The subject’s information collected during the trial will be depersonalized and protected by password, and access to data will be restricted to the trial staff by accordance with current Italian law. The complete final dataset will contain no identifying participant information, and its access will go only to the trial staff personnel.

Blood samples will be stored in the IRCCS INRCA secure facility at − 80 °C, with measures taken to ensure that specimens are kept under correct conditions always when it is stored. The expert staff that has been specially trained in sample storage and transportation would ensure that regularity issues are properly handled. With the approval of the principal investigator, the samples stored in the storage facility may be disposed of by the sample custodian. A sample disposal sheet will be completed and kept for further reference.

### Dissemination of study findings

The results of the above study will be published in local and international, peer-reviewed journals and presented at international conferences and clinical meetings.

### Ethical approval

The protocol (version 3_20-Dec-2017) study has been approved by the Ethics Committee of the IRCCS INRCA, Ancona, Italy, on 21 December 2017 (reference number: INRCA 17018). Before recruitment, the physician will give the participants complete information about the study and will provide them to sign the consent form, which has already been approved by the Ethics Committee. The model consent form and other related documentation to the participants are available from the corresponding author on request. Any possible protocol modification will be communicated to the ethical committee and to all relevant parties. Participants will also be informed that they can withdraw their consent to participate at any time and for any reason. If there will any harm to the participants of the trial, they will be compensated by the hospital’s insurance. The trial is retrospectively registered on 5 February 2019 under the Australian New Zealand Clinical Trials Registry (reference number: ACTRN12619000170123). The study will be conducted in compliance with the Declaration of Helsinki and the Good Clinical Practice (GCP) guidelines.

## Discussion

Our study describes the protocol of a clinical trial, designed for evaluation of the effects of a new dietary supplement on total cholesterol levels in patients with mild hypercholesterolemia. Randomized controlled trials (RCTs) are the “gold standard” of clinical trials, valued for their precision and robustness in assessing the impact of a nutraceutical or a food-based compound on specific diseases or related risk factors. RCTs are ideal tools for the investigation of causes and effects relationships between an intervention and a health outcome.

According to guidelines, patients with mild-hypercholesterolemia at low-to-moderate cardiovascular risk, and who perform regular physical activity and follow a healthy diet, may be treated with cholesterol-lowering functional foods or nutraceuticals to help achieve target LDL-c levels [22]. Moreover, even if the statins are the reference drug for the prevention of cardiac events associated with hyperlipidemia, an increasing number of patients refuse to use it for their possible collateral effects. The increasing availability of nutraceutical substances for the treatment of mild hypercholesterolemia can contribute to delay or prevent the use of statins. Previous studies have already explored the single beneficial effects of natural compounds, such as *Citrus bergamia*, olive tree polyphenols, phytosterols, and vitamin K2 on cholesterol levels and atherosclerosis process prevention [4, 8, 10–12]. Moreover, the effects of each these single substances on cardiovascular risk factors reduction have been studied in several RCT [23–26]. However, the synergistic effects of all these compounds were not previously tested. This is the first randomized controlled trial evaluating the effects of the intake of a new mixture of these active ingredients (BruMeChol™) in patients with mild hypercholesterolemia.

We have chosen as an experimental design a double-blind, placebo-controlled, parallel group clinical trial since it is the gold standard for assessing the cause–effect relationship of an innovative nutraceutical on selected biological parameters. Codified information about the intake of the dietary supplement or placebo for both sides, patients and physicians as well, is the best way to avoid possible bias.

On the other hand, this RCT offers many advantages for patients recruited, including the lipoproteins profile for CVDs prevention and a complete check-up. The unbalance of the lipid profile is a complex phenomenon dependent on the interaction between lifestyle and genetic make-up. This study was planned to monitor physical activity through a dedicated questionnaire, to complete the beginning and the end of the study to avoid possible bias associated with lifestyle changes. Unifying biochemical, clinical, and data originating from medical history and physical activity questionnaire, this study gives a comprehensive picture of the lipid profile of the patients.

Even if the body weight will be recorded during the study, the weak point of this trial could be that a nutrition-dedicated questionnaire is missing. ESC/ESA guidelines contain a list of foods and nutraceutical compounds that has lipid-lowering effect being explored in randomized, controlled clinical trials [27]. Finally, this protocol study planned to verify the effects of BruMeChol™ dietary supplementation in subjects with mild hypercholesterolemia could also contribute to new study designs for next large-scale multicenter clinical trials. This kind of clinical trials is necessary to be done not only to study potential synergistic effects of a new mixture of natural compounds but also to investigate its safety.

### Trial status

Patient recruitment stage (study protocol version 3_20-Dec-2017). Patient recruitment has been started on 6 March 2018. The recruitment will be completed approximately on the end of the month of July 2020.

## Data Availability

Not applicable

## Abbreviations

CVDs: Cardiovascular diseases
Il: Interleukins
miRs-21: MicroRNAs-21
LDL: Low-density lipoprotein
*hs*-CRP: High-sensitive C-reactive protein
CV: Cardiovascular
CKD-EPI e GFR: Calculation of estimated glomerular filtration rate by CKD-EPI equation
AST/GOT: Aspartate aminotransferase glutamic oxaloacetic transaminase
ALT/GPT: Alanine aminotransferase/glutamic pyruvic transaminase
HDL: High-density cholesterol
WBCs: White blood cells
RBCs: Red blood cells
MCV: Mean cell volume
MCH: Mean corpuscular hemoglobin
MCHC: Mean corpuscular hemoglobin concentration
RDW: Red cell distribution width
CK: Creatine kinase
ECG: Electrocardiography
TSH: Thyroid-stimulating hormone
Lp(a): Lipoprotein(a)
CRF: Case report form
IPAQ-SF: International Physical Activity Questionnaire
CRP: C-reactive protein
GCP: Good clinical practice
